### Recruitment of general practices

Expressions of interest will be sought from general practices across Ireland through the Health Research Board (HRB) Primary Care Clinical Trials Network Ireland (CTNI) (*n* = 146 practices) and other networks known to the research team including; the Irish Practice Nurse Association (*n* = 1800 nurses), GP collaborators and discussion fora, national diabetes primary care initiatives (*n* = 79), the Irish Diabetes Nurse and Midwife Specialist Association, and social media posts. These networks are not mutually exclusive. Eligible practices will be required to have an electronic health record system and a practice nurse, to ensure they can deliver the intervention. Eight general practices will be purposively sampled from the list of interested eligible practices. As this is a pilot trial, a formal sample size calculation is not required [51]. A sample of eight was selected based on the resources available to conduct the pilot. The sample size is generally not a requirement of pilot studies [51]. The GP partner(s) will read an information sheet and provide consent on behalf of the practice.

#### People with diabetes

Inclusion criteria include the following:
Aged 18 years or overHave diagnosed diabetes (type 1 or type 2)Are eligible to attend the national screening programme but have not attended the screening service (i.e., recently in the past 12 months or ever)

Individuals will be excluded if they have attended the DRS programme recently (i.e., in the last 12 months) or are known to be having retinopathy treatment.

### Allocating practices to trial groups

Given the investment of time and resources required to deliver the intervention, the number of clinical staff at the practice may influence the implementation and effectiveness of the intervention. Therefore, to achieve variations of experience, practices will be randomly allocated (using computer-generated random number (Excel system hosted in University College Cork)) to intervention or waitlist control groups in the ratio 1:1 following stratification by practice size (i.e., single/two-handed or group practice (≥ 3 GPs)). In order to reflect the distribution of GP practices nationally (52% with ≥ 3 GPs working) [52]. The invitation to take part in the study will be issued to the eight purposively selected practices by a member of the research team before randomisation sequencing. Due to pragmatic reasons, researchers will not be blinded to a group allocation of participating practices. Given the nature of the intervention, it will not be possible to blind participating practices.

### IDEAs intervention

The intervention will operate at the professional and provider level comprises training, audit and feedback, health care professional prompts, reimbursement for practices, and a GP-endorsed reminder for patients with information leaflet-delivered opportunistically face-to-face and systematically by phone and letter (Fig. 2). These components map to strategies proposed by Powell et al. [53] and support practice staff to deliver intervention components which target patients who have not attended screening previously (Table 2). The intervention incorporates a number of behaviour change techniques. The content of the intervention was developed using a theory-based four-stage process outlined by French et al. [54], drawing on qualitative research on the barriers and enablers of screening attendance (interviews with patients and health care professionals in Ireland) and an international systematic review of barriers and enablers of screening attendance [29, 54–56]. The acceptability and feasibility of intervention components were established through a consensus process with people living with diabetes and health professionals involved in diabetes care. Full details of the development of the intervention are in preparation for publication [57]. More details on the intervention content are provided in Additional file 1.

**Fig. 2 Fig2:**
[figure not shown]
Overview of provider and patient level intervention components and study outcomes

**Table 2 Tab2:** Professional and patient level intervention components

Strategy according to ERIC^a^ [53]	Component
Audit and provide feedback	Practice audit of patients with diabetes (type 1 or type 2)
Conduct educational meeting	Briefing and training Briefing by the researcher for the practice team Training by researcher for the staff member responsible for conducting the audit
Provide local technical assistance	Supporting materials in the form of an audit and intervention manual
Remind clinicians	Electronic prompts Laminated script for face to face or phone encounters
Use other payment schemes	Reimbursement to practices
Intervene with patients	Reminder messages delivered face-to-face or via phone GP-endorsed reminder letter and information leaflet

^a^Experts’ recommendations for implementing change project

#### Audit and provide feedback

A staff member at each participating practice (administrator or practice nurse) will be assigned within the practice to conduct an audit of their patients with diabetes (type 1 or type 2) aged ≥ 18 years. This audit is necessary as RetinaScreen does not provide registration and attendance data at the practice level. Patient’s individual records will be checked by the practice staff member for a ‘results’ letter from the national screening programme to identify all people who have not attended the screening with the national programme. Patients may be classified as follows:
‘Attenders’, patients who have any letter from RetinaScreen, i.e., the results’ letter indicating previous attendance at some time‘Recent non-attender’, i.e., they may have a results letter(s) for older appointment(s) (more than 12 months ago) but have either a Did Not Attend (DNA) letter for their last appointment or no letter in the past 12 months‘Non-attender’, i.e., DNA letter(s) and/or no results letter(s)‘No record’, i.e., no record on file; status to be verified

If there is no evidence (e.g., letter) on the patient file to indicate they are registered with the national screening programme, the staff member will verify their status through the dedicated national telephone line or online portal. Practices will be asked to complete the first step of the audit within a maximum of one calendar month. Practices with large numbers of people with diabetes may not have the capacity to audit all their patients. Therefore, practices which have > 100 patients with diabetes will be asked to audit a random sub-sample of 100 patients. They will receive advice and support from the research team on this process. They will be asked to record the total number of patients with diabetes and retain a file with some basic demographic information (age, gender, type of diabetes) to examine whether the audited sub-sample is different from patients who were not sampled. The baseline audit will be completed within one calendar month of starting the trial. At 6 months, practices will re-audit eligible patients. As the 6-month period is insufficient for all patients to attend and receive a confirmation letter from RetinaScreen, practices will also verify their status via phone call, i.e., to determine whether they (a) intend to contact RetinaScreen, (b) have contacted RetinaScreen or (c) have attended the screening. If they do not fulfil (a), (b) or (c), then, they will be asked why, and this information is recorded on the audit file. Audit data will be made available to study researchers after it has been fully anonymised at the practice.

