#### Educational meeting and provision of local technical assistance

Before the audit of patients with diabetes, the staff member responsible for conducting the audit will receive one-on-one training from a study researcher. Technical assistance with the audit will be provided by the researcher in the form of an audit manual. Training duration is estimated to take 1 h but is expected to vary according to practice experience conducting an audit. This training will be preceded by a brief, 20–30 min session on the intervention and its delivery. This session should be delivered to the entire practice team if possible. The researcher will outline the estimated time each intervention component is expected to take. For example, the audit has been piloted in a large primary care centre as part of previous work by the research team and is estimated to take on average 5 min per patient. GP collaborators on the research team have conducted a pilot (e.g., 2–3 patients) using the audit protocol to check clarity, usability and time required.

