### Control practices

In control practices, data collection will be carried out at 6 months, using date-restricted data extraction from the electronic medical record to capture data for the full 12-month period prior to the intervention, so this includes baseline and 6 months of follow-up data. This will match the 6-month period in intervention practices, during which they will have acted as control practices. This will ensure we have comparative data collection prior to the delivery of the intervention to the control group on study completion. This approach was chosen as collecting data at baseline (i.e., 6 months before study start) would constitute an intervention in those practices; knowledge of non-attenders would lead to a change in usual care as the control group would likely follow-up patients immediately. Control practices will receive the same supports and training as intervention practices to facilitate the audit feedback loop.

Implementing the patient-level intervention will not require alteration to usual diabetes care (including the use of any medication). Usual care will continue for both trial arms.

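### The eligible cohort is ascertained at different times and by different methods in the two arms, with no common index date, so the two six-month periods are not sure to match

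*Protocol article*

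**What the plan says.** **Eligibility.** Under People with diabetes, adults with diagnosed diabetes who have not attended are included, and "Individuals will be excluded if they have attended the DRS programme recently (i.e., in the last 12 months". The date from which the 12 months are counted is not stated.

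**Intervention practices.** Under Educational meeting and provision of local technical assistance, the order is briefing, training, audit: "This training will be preceded by a brief, 20–30 min session on the intervention and its delivery", and "Before the audit of patients with diabetes, the staff member responsible for conducting the audit will receive one-on-one training from a study researcher". Of the briefing it says "This session should be delivered to the entire practice team if possible". Under Audit and provide feedback, "The baseline audit will be completed within one calendar month of starting the trial". The audit produces the list of non-attenders to which prompts are attached (Remind clinicians). For follow-up, "At 6 months, practices will re-audit eligible patients".

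**Control practices.** Nothing is collected until month 6. Data are then obtained "using date-restricted data extraction from the electronic medical record to capture data for the full 12-month period prior to the intervention", and this is said to cover baseline plus six months of follow-up and to match the intervention arm's six-month period. The reason given for not auditing at baseline is that "knowledge of non-attenders would lead to a change in usual care as the control group would likely follow-up patients immediately".

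**Use of the data.** Registration and attendance are among the primary outcomes (Outcomes). The data are to supply the intervention effect for the definitive sample size (Quantitative analysis). Increases in registration and in attendance or intention to attend form a continuation criterion (Table 1).

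**The concern.** The arms are compared on cohorts built by different rules after allocation. One is formed going forward, by staff reading files as they stand at some point in the first month. The other is formed looking back from month 6, with a date restriction that is stated for control practices only.

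The same patient can therefore be treated differently by arm. Take someone who attends in week two. If an intervention practice reads the file in week four and finds a results letter, that person may be classed as a recent attender and never enter the cohort. In a control practice, reconstructed as of trial start, the same person is a baseline non-attender who attended during follow-up.

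At stake is the descriptive between-arm difference, which is carried into the definitive trial's sample size and into the steering committee's judgement on uptake.

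**Working it through.** **The plan's own figures.** The footnote to Table 1 gives 712 patients for 60% v 70%, 80% power, α = 0.05 (taken as two-sided). Per arm: [1.960·√(2·0.65·0.35) + 0.842·√(0.60·0.40 + 0.70·0.30)]² / 0.10² = (1.322 + 0.565)² / 0.01 ≈ 356, so 712 in total. It reproduces and does not change here. It supplies the yardstick, a 10-point difference. The Sample size section expects 18 eligible patients per practice, so 4 × 18 = 72 per arm.

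**Model for early attenders, with no true effect.** All three inputs are assumptions:
- u: six-month uptake, spread evenly over the six months
- t: months from trial start to the reading of the file (the protocol allows up to 1)
- v: share of early attenders whose letter is on file when the file is read

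It is also assumed that the intervention audit judges eligibility on the day of reading and the control extraction judges it at trial start.

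Fraction excluded from the intervention cohort: e = u·(t/6)·v. Intervention arm reads (u − e)/(1 − e); control reads u.

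| u (control reads) | t = 1, v = 1 | t = 0.5, v = 1 (or t = 1, v = 0.5) | t = 0.5, v = 0.25 |
|---|---|---|---|
| 6% | 0.050/0.990 = 5.1% (−0.9) | 0.055/0.995 = 5.5% (−0.5) | 0.05875/0.99875 = 5.9% (−0.1) |
| 12% | 0.100/0.980 = 10.2% (−1.8) | 0.110/0.990 = 11.1% (−0.9) | 0.1175/0.9975 = 11.8% (−0.2) |
| 24% | 0.200/0.960 = 20.8% (−3.2) | 0.220/0.980 = 22.4% (−1.6) | 0.235/0.995 = 23.6% (−0.4) |

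Differences in points, taken before rounding. With v = 0 the difference is 0. In the first column the patients lost out of 72 are 72e = 0.7, 1.4 and 2.9. At higher uptake the same ceiling is 4.3 points (u = 40%, reads 35.7%) and 4.4 points (u = 60%, reads 55.6%).

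**Opposite direction.** Suppose f patients attended just before trial start, have no letter on file at the audit, enter the intervention cohort and are counted as attended when the letter arrives. With N = 72 the arm reads (uN − eN + f)/(N − eN + f). This equals u when f = eN, so each false entry cancels one lost early attender. If f exceeds eN, the sign turns. For illustration, with u = 12%, t = 1, v = 0.5 (eN = 0.72) and f = 2: (8.64 − 0.72 + 2)/(72 − 0.72 + 2) = 9.92/73.28 = 13.5%, a spurious surplus of 1.5 points. Longer letter lag lowers e and raises f. The documents give no lag, so the net sign cannot be fixed.

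**With one index date in both arms and status taken from attendance dates,** e = 0 and f = 0, and the difference from this source is 0.

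**The case against.** The strongest reply is that the mechanism is inferred. The protocol does not say that intervention practices judge eligibility on the day a file is read. The audit manual is not shown, and a start-date cut-off in it would remove the problem. The ceiling is also generous. One month is a maximum, and at the stated 5 minutes per patient the audit takes about 5 hours for 60 patients and 8.3 for 100. The protocol itself concedes that six months is too short for every patient to attend and have a confirmation letter. An early attender without a letter stays in the cohort and later counts as a success, as in control. The outcome analysis is descriptive, the uptake criterion has no numerical threshold, and delaying control data collection is a reasoned choice.

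Most of this stands as a limit on size and direction. It does not remove the difference in procedure, which the article states. The reason for not auditing control practices at baseline is sound, but it does not stand in the way of a common index date. Letter lag adds a second asymmetry: by month 6, control files should hold letters for visits just before trial start that intervention files may have lacked at the audit.

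Four stronger readings are tempting, and the documents do not support them:
- **A demonstrated bias against the intervention.** This needs reference dates and letter timings that are not given.
- **Attendance prompted by the team briefing is lost.** Patient-level components start only after the audit is complete and prompts are added. Nothing shows that briefing staff would produce attendance and a filed letter before then.
- **New diagnoses swell the control denominator.** The extraction is date-restricted, a cohort as of trial start would leave such patients out, and no incidence figure is given.
- **The usual-care rate is distorted.** Under the early-attender mechanism control reads u, which is correct.

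**Conclusion.** The point holds as a cheap improvement. The two cohorts are ascertained at different times and by different methods after allocation, no common eligibility date is stated, and the claimed match of the six-month periods is therefore not secured.

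The early-attender effect is bounded by about 1 to 3 points against the intervention for assumed uptake of 6 to 24%, with files read at one month and all letters filed. It is about half that with a two-week audit or half the letters filed, and near zero with few letters filed. Late letters can offset or reverse it. Against a 10-point target this is modest, and it bears on an exploratory estimate, but that estimate is carried forward and the repair costs almost nothing.

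**What to change.** 1. Set trial start as the single index date for all eight practices.
2. Before allocation is disclosed, have each practice save its list of adults with diabetes and, where there are more than 100, draw the random 100 from it. Screening status is not looked at, so no non-attenders are revealed and the stated worry about changing usual care in control practices is respected.
3. In both arms, judge eligibility and outcome by attendance date relative to the index date, not by whether a letter is on file when the record is read. For control practices this means the extraction must reach 12 months before the index date as well as 6 months after it, 18 months in all.
4. Keep patients who attend between the index date and the audit in the intervention cohort, recorded as attended. Leave out, in both arms, patients who join or are diagnosed after the index date.
5. Reconcile the text under People with diabetes, Audit and provide feedback, and Control practices with these rules.

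Cost: one saved record search per practice and a change to the audit manual. The downside is a few minutes of baseline work in control practices. No extra patients are needed, and the 712 is unaffected.

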#### Educational meeting and provision of local technical assistance

Before the audit of patients with diabetes, the staff member responsible for conducting the audit will receive one-on-one training from a study researcher. Technical assistance with the audit will be provided by the researcher in the form of an audit manual. Training duration is estimated to take 1 h but is expected to vary according to practice experience conducting an audit. This training will be preceded by a brief, 20–30 min session on the intervention and its delivery. This session should be delivered to the entire practice team if possible. The researcher will outline the estimated time each intervention component is expected to take. For example, the audit has been piloted in a large primary care centre as part of previous work by the research team and is estimated to take on average 5 min per patient. GP collaborators on the research team have conducted a pilot (e.g., 2–3 patients) using the audit protocol to check clarity, usability and time required.

#### Remind clinicians

After the audit has been completed, feedback (i.e., a list of patients who have not attended screening) will be used by an assigned staff member to add electronic delivery prompts to the records of eligible patients. This will act as a reminder to prompt professionals (GPs or practice nurses) to deliver the face-to-face reminder message to patients and to record delivery of this message. Health care professionals will be asked to delete the alert if the intervention components (i.e., brief messages, leaflets) were delivered where the functionality to capture action or inaction on the alert exists in the GP software this will be utilised.

#### Payment scheme

Practices will be reimbursed for the cost of taking part in training, conducting the audit and delivering the intervention, including any consumables. Practices will be paid a fee (a maximum of €1000 per practice) based on estimated salary costs, time to deliver the intervention and allowances for overheads. Practices will be reimbursed at the start of the study (€500) and upon receipt of the audit file at study completion (maximum of €500) by the research team.

#### Intervene with patients to enhance uptake and adherence

The patient-level intervention consists of reminders delivered opportunistically face-to-face, and systematically by phone and letter accompanied by an information leaflet. These components will be delivered after the audit has been completed and prompts added to electronic records.

##### Verbal reminders

All eligible patients will receive a phone call from a practice nurse, reminding them to attend the screening. Nurses who deliver the phone call will follow a short script (Additional file 2) and inform the patient they will receive a follow-up letter with more information. At this point, the patient status will also be updated on the audit file and electronic patient record, for example, if the patient is attending another service for screening (e.g., ophthalmologist). This will enable staff to shortlist patients who should receive the letter. In-person reminders will be delivered opportunistically by GPs and practice nurses if an eligible patient attends for an appointment during the 6-month trial period. They will follow the short script (Additional file 2) and provide patients with a standard information leaflet (Additional file 3).

##### GP-endorsed letter and information leaflet

Following the phone call, patients will receive a reminder letter, recommending participation in the national retinopathy screening programme, together with key messages (Additional file 2). A copy of the consent and registration form developed by RetinaScreen, a freepost envelope, and the information leaflet will be included with the letter.

Reminders will be issued to patients during a 2-week period following the audit. During this time period, it will be specified that the practice should make a reasonable attempt (i.e., three attempted phone calls) to remind patients using the approaches outlined, after which the letter should be issued.

All materials have been designed to be understood by readers with low literacy, numeracy or both, with input from healthcare providers and patients. Materials have been reviewed by the National Adult Literacy Agency and the IDEAs Patient and Public Involvement (PPI) group.

### Control practices

In control practices, data collection will be carried out at 6 months, using date-restricted data extraction from the electronic medical record to capture data for the full 12-month period prior to the intervention, so this includes baseline and 6 months of follow-up data. This will match the 6-month period in intervention practices, during which they will have acted as control practices. This will ensure we have comparative data collection prior to the delivery of the intervention to the control group on study completion. This approach was chosen as collecting data at baseline (i.e., 6 months before study start) would constitute an intervention in those practices; knowledge of non-attenders would lead to a change in usual care as the control group would likely follow-up patients immediately. Control practices will receive the same supports and training as intervention practices to facilitate the audit feedback loop.

Implementing the patient-level intervention will not require alteration to usual diabetes care (including the use of any medication). Usual care will continue for both trial arms.

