**Methods:**

The IDEAs study is a cluster randomised pilot trial with an embedded process evaluation and economic evaluation. Following stratification by practice size, eight general practices (clusters) will be randomly allocated to intervention (*n* = 4) or wait-list control groups (*n* = 4). The intervention will be delivered for 6 months, after which, it will be administered to wait-list control practices. The intervention is multi-faceted and comprises provider-level components (training, audit and feedback, health care professional prompt, reimbursement) and patient-level components (GP-endorsed reminder with information leaflet delivered opportunistically face-to-face, and systematically by phone and letter). Patient inclusion criteria are type 1 or type 2 diabetes and DRS programme non-attendance. A multi-method approach will be used to determine screening uptake, evaluate the trial and study procedures and examine the acceptability and feasibility of the intervention from staff and patient perspectives. Quantitative and qualitative data will be collected on intervention uptake and delivery, research processes and outcomes. Data will be collected at the practice, health professional and patient level. A partial economic evaluation will be conducted to estimate the cost of delivering the implementation intervention in general practice. Formal continuation criteria will be used to determine whether IDEAs should progress to a definitive trial.

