## Background

Diabetes mellitus (diabetes) places a significant burden on health systems, largely attributable to the complications associated with the condition [1, 2]. The number of people with diabetes is growing worldwide, with type 2 diabetes accounting for approximately 90% of all cases [2]. Diabetic retinopathy (DR) is the most common microvascular complication of diabetes and a leading cause of blindness among people of working age in many countries [3, 4], including Ireland [5]. Worldwide, it is estimated that approximately 28 million individuals have vision-threatening retinopathy [6]. Visual impairment due to retinopathy can negatively impact on an individual’s quality of life and ability to self-manage which can lead to other complications [7].

Diabetic retinopathy screening (DRS) leads to earlier detection of pre-symptomatic retinopathy and treatment to prevent or delay the development of diabetes-related blindness. Screening for retinopathy is effective in reducing the risk of vision loss [8] and is cost-effective [9, 10]. National and international guidelines recommend annual DRS for people with diabetes [11–13]. Despite evidence for the effectiveness of DRS, uptake continues to be sub-optimal in many countries [14–17]. The current uptake of the national DRS programme in Ireland, in operation since 2015, is approximately 56% [18]. In England, where a national DRS programme has been established for > 10 years, attendance rates vary from 71–91% [19, 20]. Non-attendance for screening has been identified as a risk factor for poor visual outcomes among those with diabetes [21]. Non-attendance is also costly for the health service; retrospective analysis of 1 year of missed appointments within a primary care organisation in the UK was calculated to cost £78,259 [22].

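### As written, the control-arm extraction holds 6 months of record before baseline where the non-attendance rule needs 12, so some recent attenders would count as eligible in control practices only

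*Protocol article*

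**What the plan says.** **Eligibility.** Under Recruitment of general practices, People with diabetes, a patient must "have not attended the screening service (i.e., recently in the past 12 months or ever". The exclusion mirrors this: "Individuals will be excluded if they have attended the DRS programme recently (i.e., in the last 12 months". The Audit and provide feedback section uses the same look-back to define a recent non-attender, of whom it says "they may have a results letter(s) for older appointment(s) (more than 12 months ago".

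**Intervention practices.** Staff check each record for results letters, and no date limit is stated. On timing: "The baseline audit will be completed within one calendar month of starting the trial".

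**Control practices.** "In control practices, data collection will be carried out at 6 months, using date-restricted data extraction from the electronic medical record". The purpose is "to capture data for the full 12-month period prior to the intervention, so this includes baseline and 6 months of follow-up data". The stated reason for waiting is that a baseline audit would itself prompt staff to follow up non-attenders. The Abstract places the end of the control period: "The intervention will be delivered for 6 months, after which, it will be administered to wait-list control practices".

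**Use of the data.** Attendance is one of the primary outcomes. Table 1 uses the numbers attending or intending to attend in a continuation criterion. The Quantitative analysis section takes the effect estimate forward to the sample size of the definitive trial.

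**The concern.** The control window has to do two jobs: establish who was a non-attender at baseline, and record who attended in the following six months. Twelve months of record cannot do both under a 12-month rule.

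Take a patient screened nine months before baseline. In an intervention practice the letter is seen and the patient is excluded. In a control practice the letter lies outside the window, so the patient enters the denominator as a non-attender. The Background says "National and international guidelines recommend annual DRS for people with diabetes", so a patient who keeps to that interval falls due about three months into follow-up and is then counted as control uptake.

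The two arms would therefore build their denominators by different rules, and the error runs against the intervention. A six-month look-back also cannot separate control patients who never attended from those who attended and lapsed.

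**Working it through.** **1. The plan's own figures.** From Sample size and the notes to Table 1:
- Patients with diabetes per practice: 1200 × 0.05 = 60.
- Not registered: 0.20 × 60 = 12, leaving 48 registered.
- Eligible among the registered: 48 × (0.34 + 0.03) = 17.8, stated as 18.
- Definitive trial, 60% against 70%, 80% power, two-sided 0.05 without continuity correction: 356 per arm, 712 in total, as stated; 712/18 = 39.6, about 40 practices.

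These reproduce, and the window problem does not affect them.

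**2. The window.** Put baseline at month 0. Control practices receive the intervention after month 6, so the 12 months before it run from month −6 to month +6.
- Record available before baseline: 12 − 6 = 6 months.
- Record needed by the eligibility rule: 12 months (month −12 to 0).
- Record needed for eligibility and follow-up together: 12 + 6 = 18 months.
- Gap: month −12 to month −6.

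Moving the rule to the extraction date does not help. Excluding everyone who attended in the 12 months before month +6 would remove every control patient who attended during follow-up and set control uptake to zero.

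**3. How many patients (illustration).** Registered patients not counted as eligible: 48 − 18 = 30. Assume that all 30 attend yearly and that visits are spread evenly. Half, 15, were then last seen in the gap. The correct denominator is 18, or 30 if the 12 unregistered patients are included.
- 15/(18 + 15) = 15/33 = 45% wrongly included.
- 15/(30 + 15) = 15/45 = 33% wrongly included.

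If 25% to 75% of the 30 fall in the gap (7.5 to 22.5 patients):
- base 18: 7.5/25.5 = 29% to 22.5/40.5 = 56%;
- base 30: 7.5/37.5 = 20% to 22.5/52.5 = 43%.

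**4. Effect on control uptake.** Let s be the share wrongly included, r the proportion of them who return in follow-up, and p the true control uptake. Apparent uptake is (1 − s)p + sr, so the rise is s × (r − p). The protocol gives neither r nor p; assume p = 10% and r = 60% to 100%.

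| Denominator | s | Rise at r = 60% | Rise at r = 100% |
|---|---|---|---|
| 45 | 0.333 | 0.333 × 0.5 = 17 points | 0.333 × 0.9 = 30 points |
| 33 | 0.455 | 0.455 × 0.5 = 23 points | 0.455 × 0.9 = 41 points |

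For comparison, the effect assumed for the definitive trial is 70 − 60 = 10 points.

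**The case against.** **Older letters stay on file.** Control practices get the same training and support as intervention practices, the Outcomes section describes measurement by practice audit without distinguishing arms, and the audit manual and the schedule figure are not available here. A reader might infer that control eligibility cannot be established at all. The protocol does not support that: the letters exist, and the manual may tell staff to use them. But no section gives control practices a longer look-back, and the extraction is expressly restricted by date. The inconsistency in the text stands.

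**The window could mean 12 months before trial start.** That would give the full look-back, but the same sentence places the six follow-up months inside the twelve.

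**The numbers are soft.** This is largely right. The protocol does not say that the other 30 registered patients attended in the past year or attend yearly; some may be lapsed attenders who are eligible anyway. Full return within follow-up is an upper bound. The audit section itself accepts that six months is too short for every patient to attend and have a letter on file, and the attendance outcome relies on that letter.

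**Stronger readings to avoid.**
- That all annual attenders enter the control denominator: those seen in months −6 to 0 are still excluded correctly.
- That the rise is simply share × return rate (20 to 45 points): this holds only if true control uptake is zero, which nothing in the protocol states.
- That the arms have materially different index dates: the one-month limit is a deadline for completing the audit, not a statement of when status is fixed, and the difference would be a month at most.

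**It is a pilot.** The outcome analysis is descriptive, the uptake criterion has no numeric threshold and is left to the Trial Steering Committee's judgement, and the number eligible per practice can still be taken from the four intervention practices. This limits the harm but does not remove it, because the effect estimate is carried forward.

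**Conclusion.** The point holds. The extraction as written supplies 6 of the 12 months of record needed before baseline, and this follows from the protocol's wording alone. Its direction is also clear: control patients last screened 6 to 12 months before baseline are wrongly included, and those who return on schedule raise control uptake.

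The size is illustrative. Under yearly, evenly spread attendance by the 30 patients, a third to just under a half of the control denominator would be wrongly included (20% to 56% over the wider range). With 10% true uptake and 60% to 100% return, the rise is about 17 to 41 points across the two denominators. Fewer yearly attenders, lower return or late letters would each reduce it.

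No hypothesis test is invalidated. What is at risk is the control rate and the between-arm difference used for the continuation decision and for planning the definitive trial: an effective intervention could look ineffective.

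**What to change.** In the Control practices section, replace the 12-month window with at least 18 months: 12 before the index date plus 6 of follow-up. Preferably, use all results letters on file, as in the intervention audit, which also lets never-attenders be separated from lapsed attenders. State one index date for both arms and apply the 12-month rule from letter dates at that date. Carry the same wording into the audit manual.

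The extraction remains retrospective at month 6, so the reason for not auditing control practices at baseline is respected. The cost is a longer date filter and slightly more record checking in four practices. It should be settled before extraction, because the data are anonymised in the practice before release and the research team could not restore the missing look-back itself.
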